### Sample size

Based on a preliminary internal investigation and insights of healthcare professionals working in the AAW, the proportion of the control group that is safely discharged was estimated to be 40%. As an increase to 50% was deemed to be feasible and clinically relevant, this proportion was used for the sensor group in calculating the sample size. The aim is to reject the null hypothesis stating that the proportion of patients that are discharged home safely directly after AAW stay is equal in the control and sensor groups. With a power of 80%, an *α* of 0.05, and equal group sizes, a total of 768 participants are required [19]. To achieve this number of patients with an assumed drop-out rate of 5%, the sample size is set to 800 patients, i.e., 400 in the control group and 400 in the sensor group.

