### Statistics

For the descriptive analyses (e.g., characteristics of participants), continuous variables will be reported as mean with standard deviation for normally distributed data, and median with interquartile range for non-normally distributed data. For categorical variables, numbers and percentages will be reported.

For the primary outcome, the proportion of patients discharged home safely, directly after AAW stay, will be compared between the control and sensor group using a chi-squared test. Differences in LOS will be tested using Student’s *t*-test or Mann-Whitney test depending on the presence of a normal distribution. To assess whether the percentages of ICU admissions, RRT calls, and hospital admissions differ between the control and sensor groups, chi-squared or Fisher’s exact tests will be used, as appropriate. Intention-to-treat analyses will be used for the primary and secondary outcomes. Additionally, per-protocol analyses will be used to assess the effect of the sensor, adjusted for patients who receive a non-functional sensor due to technical reasons. All remaining patients will be included in these per-protocol analyses, regardless of their destination after AAW admission and the duration for which the wearable sensor was worn. An interim analysis for futility is planned once 50% of total amount of patients is included.

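### 800 patients less 5% drop-out leaves 760, not the required 768: a minor slip of about half a point of power, in an 80% figure that also leaves out the planned futility look

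*Protocol article*

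**What the plan says.** The Sample size section of the protocol article gives the design inputs. For the control group, "the proportion of the control group that is safely discharged was estimated to be 40"%. For the other arm: "As an increase to 50% was deemed to be feasible and clinically relevant, this proportion was used for the sensor group". With 80% power, an alpha of 0.05 and equal arms, "a total of 768 participants are required". The next sentence adds the allowance for losses: "To achieve this number of patients with an assumed drop-out rate of 5%, the sample size is set to 800 patients", split as 400 per arm.

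The Statistics section names a chi-squared test for the primary outcome, analysed by intention-to-treat, and adds: "An interim analysis for futility is planned once 50% of total amount of patients is included". The Sample size section does not mention this look.

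Under Outcomes, success requires direct discharge from the acute admission ward followed by 30 days without unplanned readmission, emergency department revisit or death.

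**The concern.** The allowance for drop-out is presented as the step that turns 768 analysable patients into 800 randomised ones. It does not do so at the stated rate, and the two sentences stand side by side, so no other document can make 768, 5% and 800 agree.

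Secondly, 80% is the power of a trial with a single final analysis, whereas this trial plans a futility look at half the patients. A futility-only look does not inflate the type I error, but a stop that is acted on can only lower power.

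Readers of a null result will use the stated power to judge how informative it is. The figure should match the number expected in the analysis and the design as it will be run.

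**Working it through.** **Inputs.** From the Sample size section: p1 = 0.40, p2 = 0.50, alpha 0.05, power 0.80, equal arms, 768 required, 5% drop-out, 800 randomised. From Statistics: chi-squared test, one futility look at 50% inclusion (400 patients). Sidedness is not stated. I take it as two-sided because the null hypothesis is equality; a one-sided test would need 305 per arm (610 in total), which does not match 768.

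**Reproducing 768.**
- Unpooled variance: n = (1.960 + 0.842)² × (0.24 + 0.25) / 0.10² = 384.6 per arm, 769.2 in total. Rounding down to 384 per arm gives 768.
- Pooled variance under the null, which corresponds to the chi-squared test: n = [1.960 × √(2 × 0.45 × 0.55) + 0.842 × √0.49]² / 0.10² = 387.3, so 388 per arm and 776 in total.

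The plan's 768 is therefore reproduced, within 1% of the pooled result. It is already rounded down, so it has no slack to absorb a further miss.

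**The drop-out step.**
- 800 × 0.95 = 760, which is 8 short of 768.
- 768 / 0.95 = 808.4, so 809, or 810 with equal arms.
- Even the common shortcut, 768 × 1.05 = 806.4, gives 807.
- 1 − 768/800 = 4.0%, the drop-out that 800 does cover.

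**Power by number analysed.** Unpooled: Φ(0.10 × √n / 0.70 − 1.960). Pooled: Φ((0.10 × √n − 1.960 × √0.495) / 0.70).

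| Analysed | n per arm | Pooled | Unpooled |
|---|---|---|---|
| 760 | 380 | 79.2% | 79.5% |
| 768 | 384 | 79.7% | 79.9% |
| 800 | 400 | 81.3% | 81.5% |

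Moving from 768 to 760 costs about half a point.

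**The futility look.** The article gives no boundary, so the rules below are assumptions chosen to show the range. The interim and final test statistics are treated as bivariate normal at information fraction t = 0.5 (correlation √0.5). The trial succeeds if the final Z exceeds 1.960 and it was not stopped; the rule is assumed always to be followed. With 760 analysed, the expected final Z is θ = 1.960 + 0.815 = 2.775.

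- Stop if conditional power under the design effect is below 20%: interim boundary Z = [1.960 − 2.775 × 0.5 + √0.5 × (−0.842)] / √0.5 = −0.03.
- Stop if conditional power under the current trend is below 20%: boundary Z = √0.5 × [1.960 + √0.5 × (−0.842)] = 0.965. With a 10% threshold it is 0.745.

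| Assumed rule, always followed | 760 analysed | 800 analysed |
|---|---|---|
| No look | 79.2% | 81.3% |
| Design effect, below 20% | 79.0% | 81.0% |
| Current trend, below 10% | 75.8% | 77.9% |
| Current trend, below 20% | 73.3% | 75.5% |

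The design-effect rule costs 0.2 to 0.3 points. The trend-based rules cost about 3 to 6.

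**The case against.** The best defence is that the slip has no practical weight. Half a point of power lies well inside the uncertainty of a 40% control rate taken from a preliminary internal investigation and staff opinion. The analysed number may also exceed 760. The analysis is by intention-to-treat, outcomes come mainly from the medical record, and under Recruitment the data of patients who withdraw are kept up to withdrawal unless consent is fully revoked. A transfer to an in-hospital ward fails the endpoint as soon as it happens. If all 800 are analysed, power is above the stated 80%. All of this stands, and it is why the point is minor. It does not make the sentence correct, because the plan itself assumes 5% and claims that 800 delivers 768.

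It can also be said that a journal article may leave the futility boundary, whether it is binding, and the data cut to the full protocol or analysis plan. That stands too: the missing rule is not counted as a fault here. What remains is that the printed 80% matches a calculation without a look.

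A reader might infer from the trend-based figures that the trial's real power is several points below 80%. The article does not support that. It names no trend-based rule and does not say that a stop would be binding; under a design-effect rule the loss is negligible. A reader might likewise infer that the look will be made on immature outcomes, because it is triggered by inclusion. The text can equally be read as fixing which patients the look covers, with their follow-up completed first.

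**Conclusion.** The drop-out sentence is wrong as written: 800 covers 4.0% drop-out, and 5% leaves 760. The cost is about half a point of power (79.2% to 79.5% instead of 79.7% to 79.9%), and there is none if intention-to-treat retains everyone (81.3% to 81.5%). These figures assume a two-sided 5% test without continuity correction and true rates of 40% and 50%.

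The 80% also omits the futility look. The further loss cannot be fixed from the article: it runs from 0.2 to 0.3 points under a lenient design-effect rule to about 3 to 6 points under the trend-based rules tried, if always followed. The article neither shows nor excludes a material loss. This is a minor correction to a reported figure and does not show that the trial is underpowered.

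**What to change.** Keep 800 and restate the allowance in the Sample size section, for example: 800 patients allow for 4% drop-out; with 5% drop-out (760 analysed) power is about 79%; if all 800 are analysed it is about 81%. If the 5% allowance with 768 analysed is to be kept instead, 810 patients are needed, 405 per arm.

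Quote the power with whatever futility rule the full protocol or analysis plan uses, and say whether the rule is binding. State that the look is made once the first 400 patients have complete 30-day outcomes. Otherwise transfers count as failures at once, while recent direct discharges cannot yet be counted as successes.

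The restatement costs two or three sentences and no extra patients. If the look would otherwise be made at the moment of inclusion, it comes about a month later.

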### Recruitment

When all criteria for participation are met, the patient receives verbal and written information about the trial from an emergency physician at the ED. The patient is able to consider participation and ask questions to any physician or nurse until 2 h after admission to the AAW. If a patient decides to participate in the trial, the patient signs an informed consent form. Subsequently, the patient will be allocated to either the control or sensor group. Participants cannot switch between the control and sensor groups. However, a patient is allowed to withdraw from the trial without providing a reason for withdrawal and still receives usual care. Data generated of these patients will be used for analyses until the date of withdrawal, unless a patient revokes informed consent completely.

### Randomization

This trial will employ a 1:1 randomization scheme with block sizes of four and eight, in random order, to allocate patients to either the control or sensor group. A computer-generated randomization scheme is consulted by a nurse after the patient has provided informed consent.

### Blinding

The allocation of patients is concealed from both the patient and the nurse. After allocation, both nurse and patient are aware of the patient’s allocation due to the attachment of a wearable sensor generating real-time data. Outcome assessors (SG, NK) are not blinded to facilitate study logistics. However, because the outcomes cannot be influenced by the outcome assessors, any potential bias attributable to the absence of blinding is considered negligible. Data analysts (SG, NK) are also not blinded in this trial.

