### Outcomes

The primary outcome is the difference between the control and sensor group in the percentage of patients who are safely discharged from the hospital directly after AAW stay. A safe discharge is defined as a discharge without following unplanned hospital readmission, ED revisit, or mortality within 30 days. Secondary outcomes are LOS in the AAW, LOS in the in-hospital wards, percentage of RRT calls during AAW and hospital stay, percentage of ICU admissions during AAW and hospital stay, and percentage of unplanned readmissions to the hospital within 30 days after hospital discharge. Furthermore, facilitators and barriers for implementing continuous monitoring in usual care in the AAW will be assessed by questionnaires and interviews with healthcare professionals. Also, for the sensor group, the feasibility of remote home monitoring with the wearable sensor is assessed, including the duration for which the sensor was worn, factors leading to its early detachment, user complaints regarding wearing the sensor, and restrictions in daily activities.

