### Data collection and management

Data are collected from four different sources. Firstly, data on medical treatment, laboratory tests, patient characteristics, and primary and secondary outcomes, such as whether a patient was safely discharged, are retrieved from the Electronic Medical Record (EMR). Secondly, for the sensor group, wearable sensor data of the overall period up to 14 days are collected. Thirdly, supplementary data pertaining to the primary outcome, specifically healthcare usage after discharge (e.g., readmissions in other hospitals), will be obtained from patient questionnaires. The questionnaires also include information regarding the patient’s experience with the wearable sensor to assess feasibility. Since there is currently no validated questionnaire aligned with our study objectives, self-constructed questionnaires will be employed. Fourthly, data from questionnaires and interviews with healthcare professionals are collected at the end of the trial. Healthcare professionals will be selected using a stratified sampling method, ensuring a representative distribution of all specialties that operate in the AAW. These data will be used to investigate facilitators and barriers for implementing continuous monitoring in usual care in the AAW.

All collected data are protected according to data protection standards of the Netherlands and the European Union. All EMR and wearable sensor data are stored in pseudonymized form on secured hospital databases and are only accessible by authorized persons for this project. The questionnaire data are stored in pseudonymized form using the Research Manager platform (version 5.57.0). On signing the consent form, participants agree to the utilization of their data collected until the moment of potential withdrawal. Also, they agree to share relevant data with the involved researchers from the university or from regulatory authorities. Furthermore, patients are requested to provide consent for the utilization of their data in future studies pertaining to remote healthcare. No collection of biological specimens for storage will be conducted.

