### Monitoring and dissemination

Given the previous experience with the wearable sensor [13, 14, 23], no serious adverse events or serious adverse device effects are to be expected. However, if an unanticipated serious adverse event or serious adverse device effect occurs within 30 days, the primary investigator will be notified swiftly and the incident will be documented in the patient’s EMR. In case of a safety-relevant event, the primary investigator will inform the sponsor and ethics committee of the incident within 24 h.

This clinical trial will be audited by an independent auditor to ensure the trial’s integrity. The first visit by the auditor occurs before the start of the trial. Hereafter, visits take place after the first three inclusions and every year until the trial is finished. After finishing the trial, there will be a concluding visit. During these visits, the integrity of the trial process will be assessed, and an evaluation will be conducted to ensure that the involved parties have adequately fulfilled their tasks and responsibilities. Given the perceived low-risk nature of utilizing a commercially available CE certified wearable sensor, the involvement of a data monitoring committee was deemed unnecessary. The trial steering committee, comprising representing physicians (ED, internal medicine, and anesthesiology) and researchers of different fields, will convene in monthly meetings to assess the conduct of the trial. Furthermore, daily support will be provided by two researchers, four charge nurses working in the AAW, and two ED physicians. Amendments to the protocol will be communicated with the ethical committee in accordance with the standards of the Central Committee on Research Involving Human Subjects in the Netherlands. The results will be communicated via multiple scientific publications and conference talks.

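### The Blinding section calls bias from unblinded outcome assessment negligible because assessors cannot influence outcomes, but parts of the primary outcome must be classified, and the two people who do so know the arm

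*Protocol article*

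**What the plan says.** The Blinding section states that outcome assessors "are not blinded to facilitate study logistics" and that data analysts "are also not blinded in this trial". The same two sets of initials stand for both roles. The section accepts this "because the outcomes cannot be influenced by the outcome assessors, any potential bias attributable to the absence of blinding is considered negligible".

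Under Outcomes, "A safe discharge is defined as a discharge without following unplanned hospital readmission, ED revisit, or mortality within 30 days". Unplanned readmission within 30 days of hospital discharge is also a secondary outcome.

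The data collection section takes the outcomes from the electronic medical record (EMR) and adds a second source: "supplementary data pertaining to the primary outcome, specifically healthcare usage after discharge (e.g., readmissions in other hospitals), will be obtained from patient questionnaires". These questionnaires are self-constructed.

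The article describes the discharge part of the outcome in two ways. The Abstract, Statistics and Sample size sections count patients discharged home. The Outcomes section counts discharge from the hospital directly after the acute admission ward (AAW). The Intervention section lists home, nursing home and in-hospital ward as three separate destinations.

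**The concern.** The sentence treats causing an event and classifying it as the same thing. The first is beyond the assessors' reach; the second is their task. If knowledge of the arm affects even a few classifications in one direction, the comparison of proportions is biased and a larger sample does not remove the bias. The same two people then run the test, so no later step is carried out without knowledge of the arm.

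This matters more here because the discharge decision, which is a large part of the primary outcome, is necessarily open-label. Outcome coding and the final analysis are steps that could be masked, and the article leaves them open for logistical reasons only. Its Discussion lists the lack of blinding of patients and physicians as a limitation, but not that of assessors or analysts.

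**Working it through.** **1. The plan's own figure.** Inputs from the Sample size section: 40% against 50%, 80% power, α 0.05, equal groups. Sidedness is not stated; two-sided is assumed.

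- Unpooled formula: n per arm = (0.40 × 0.60 + 0.50 × 0.50) × (1.960 + 0.842)² / 0.10² = 0.49 × 7.849 / 0.01 = 384.6. Rounded up, this is 385 per arm and 770 in total.
- Pooled formula: 388 per arm, 776 in total.
- The stated 768 (384 per arm) is within 3% of both. Power at 384 per arm is 79.7%.
- Dropout: 768 / 0.95 = 809 against the stated 800, also within 3%.

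No stated number is wrong. The point concerns a stated reason, not the sample size.

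**2. Where judgement can enter.** Components of the primary outcome, set side by side:

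| Component | Source | Room for judgement |
|---|---|---|
| Death within 30 days | EMR | Very little |
| ED revisit within 30 days | EMR | Little; counts whatever the reason |
| Left the AAW without ward transfer | EMR | Little |
| Destination counts as discharged | EMR | Yes, for nursing-home discharges: home in three sections, from the hospital in one |
| Readmission was unplanned | EMR | Yes, mainly for readmissions that bypassed the ED; the article gives no rule |
| Care elsewhere | Patient questionnaire | Yes; someone must code it and merge it with the EMR |

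The last three rows contradict the claim that assessors cannot influence the outcome. The ED-revisit component does not form part of the secondary readmission outcome, so there the unplanned label decides directly.

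**3. What a small shift would do (assumption, not a figure from the article).** Suppose there is no true effect, 40% in both arms, 384 per arm, and knowledge of the arm moves a net share m of sensor patients from not safe to safe. With p₂ = 0.40 + m and p̄ = (0.40 + p₂)/2:

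- SE₀ = √[2 p̄(1 − p̄)/384]
- SE₁ = √[(0.40 × 0.60 + p₂(1 − p₂))/384]
- Rejection probability = Φ[(m − 1.96 SE₀)/SE₁] + Φ[(−m − 1.96 SE₀)/SE₁]

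For m = 0.02: SE₀ = √(2 × 0.41 × 0.59/384) = 0.0355 and SE₁ = 0.0355. The first term is Φ(−1.397) = 0.081, the second Φ(−2.524) = 0.006, and the sum is 0.087.

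| Net shift m | Sensor patients (of 384) | Two-sided error | Of which favours sensor |
|---|---|---|---|
| 0 | 0 | 5.0% | 2.5% |
| 1 point | 3.8, about 4 | 5.9% | 4.7% |
| 2 points | 7.7, about 8 | 8.7% | 8.1% |
| 3 points | 11.5, about 12 | 13.5% | 13.2% |

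For scale, with 384 per arm and a 40% control rate the smallest significant difference is 27 patients (27/384 = 7.0 points).

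**The case against.** The strongest reply is that little is left to judge. Death, ED revisit and direct discharge are largely facts of record. Any ED revisit already makes a discharge unsafe, so the unplanned label changes the primary outcome only for readmissions that did not pass through the ED, and only among patients discharged directly. Surgery scheduled within 30 days is an exclusion criterion, which removes one obvious source of planned readmissions. The full protocol, which is not shown, may define unplanned. All of this stands. It limits the size of the problem and means that the 8 or 12 patients above may not exist. It does not repair the sentence: a small exposed share is a different argument from an outcome that assessors cannot influence, and the open dual role is stated outright.

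It is also true that masked coding cannot correct reports from patients who know their own arm. It protects only the step from report to code.

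Three stronger readings are tempting but not supported:

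- **That the missing data monitoring committee rests on the same argument.** The article says that "An interim analysis for futility is planned once 50% of total amount of patients is included" and that "the involvement of a data monitoring committee was deemed unnecessary", but the reason it gives for the latter is the low risk of a CE-certified sensor. The assessor argument is used only for unblinded outcome assessment.
- **That interim results will reach the steering committee and change enrolment or discharge.** The article does not say who performs or sees the futility analysis, and it gives the committee the task of assessing trial conduct. The full protocol may settle access. Moreover, eligibility is judged before consent and concealed allocation, so a change in who is enrolled would affect both arms alike.
- **That a bias of a particular size is shown.** No count of borderline cases appears in the article.

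**Conclusion.** The point holds in a limited form. The reason given in the Blinding section is unsound, because three elements of the primary outcome, and the secondary readmission outcome, need classification by people who know the arm. *Negligible* therefore does not follow from the reason stated. It might still be true because the exposed share is small, but the article neither argues this nor gives that share.

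The error rates of about 6%, 9% and 13% rest on an assumed one-directional net shift of 1, 2 or 3 points, no true effect, a 40% rate, 384 per arm, a two-sided test and the normal approximation. They show how much misclassification would matter, not how much is expected. A shift the other way would hide a benefit instead. The change is worth making because it is cheap and the discharge decision is already open-label, not because a bias has been demonstrated.

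**What to change.** 1. Replace the sentence in the Blinding section. State that assessors cannot cause events but do classify some of them, and describe the safeguards below.
2. Define *unplanned* by a fixed rule on EMR fields, such as admission urgency or route. Define by a similar rule which destinations count as discharge, and align the Abstract, Outcomes, Statistics and Sample size sections on whether a nursing-home discharge counts.
3. Code the remaining cases, including questionnaire-reported care elsewhere, from a pseudonymised list of post-discharge contacts with arm and sensor fields removed. Removing the fields masks only a coder who cannot recognise the patients, so someone outside the daily running of the trial is preferable to the two unblinded researchers.
4. Lock this coding before allocation is merged.
5. Run the final primary analysis on arms labelled A and B, and reveal the labels once the result is fixed.

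The data are already stored in pseudonymised form, so the work amounts to an extract without the arm and sensor fields, a short coding rule and a few sentences in the protocol. The downside is a small delay in data handling, plus some coding time from another person if one is used. The sample size does not change.
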